## Abstract

**Background:**

In the era of precision oncology, patients with advanced cancer are often living longer but are enduring years of fatiguing treatment. Fatigue is among the most common, chronic, and under-addressed side effects of advanced cancer treatment, and can lead to dose reductions, treatment interruptions, and discontinuation. Oral PolyADP-ribose polymerase (PARP) inhibitors have revolutionized the treatment of advanced ovarian cancer but are often accompanied by clinically-significant fatigue, and evidence-based treatments to cope with this side effect remain limited. A pilot trial suggests that telehealth acceptance and commitment therapy (ACT), a variant of cognitive behavioral therapy based on acceptance, mindfulness, and personal values, has potential to improve fatigue interference (i.e. disrupting activity and quality of life) among ovarian cancer patients on maintenance PARP inhibitors. This study protocol describes a fully-powered randomized controlled trial (RCT) of an innovative, remotely-delivered ACT intervention (‘*REVITALIZE*’) that aims to improve fatigue outcomes and PARP inhibitor adherence.

**Methods:**

This two-armed, prospective RCT randomizes 240 adults with advanced ovarian cancer who report moderate to severe fatigue while on PARP inhibitors 1:1 to either *REVITALIZE* or education-enhanced usual care. The *REVITALIZE* intervention includes eight weekly one-hour individual sessions delivered via videoconference, plus two booster sessions at one- and two-month intervals thereafter. Participants, recruited from both academic and community cancer care sites across three U.S. regions, will complete assessments at baseline, mid-intervention, post-intervention, and 20 and 28-week follow-up (FU). The primary patient-reported outcome is change in fatigue interference from baseline to week 20 (FU1). Secondary patient-reported outcomes include fatigue severity, catastrophizing, self-efficacy, and quality of life. The primary behavioral outcome is monthly PARP inhibitor adherence, assessed by wireless medication adherence monitors; dose interruptions, reductions, and persistence will also be evaluated using adherence monitors and medical chart review.

**Discussion:**

This paper describes a RCT that will evaluate the efficacy of the telehealth *REVITALIZE* intervention for improving fatigue-related outcomes and medication adherence among adults with advanced ovarian cancer taking PARP inhibitors. Findings will inform clinical practice and supportive care for adults with advanced ovarian cancer receiving treatments that cause fatigue.

**Trial registration:**

Clinicaltrials.gov NCT06710548 on November 29, 2024.

**Supplementary Information:**

The online version contains supplementary material available at 10.1186/s12885-026-15936-0.

## Background

Fatigue is one of the most common side effects experienced by patients with advanced cancer and is a pressing problem [1–3] that remains vastly underreported, underdiagnosed, and undertreated [4, 5]. In the era of precision oncology, novel treatments such as targeted therapies, anti-angiogenic agents, immunotherapy, and antibody-drug conjugates [2, 3] are extending survival [6–8], yet creating a growing population of advanced cancer patients who remain on treatment for years and experience clinically significant, enduring fatigue as a result. Unaddressed fatigue can compromise cancer treatment outcomes as a dose-limiting side effect or by reducing adherence to oral therapies [9]. Unlike other common treatment-related side effects (e.g., nausea, pain), pharmacologic strategies are largely ineffective at addressing fatigue [10–12]. For patients requiring ongoing maintenance treatment, it is more realistic to reduce the *interference* of fatigue on daily life (‘fatigue interference’) than eliminate fatigue altogether. However, apart from a recent breast cancer trial [13], few studies in advanced cancer have examined this outcome.

Ovarian cancer offers an ideal context to evaluate interventions to reduce fatigue interference in patients with advanced cancer. Nearly 80% of patients with ovarian cancer are diagnosed with advanced disease, stage III or IV, which is typically incurable [14]. Most patients receive 2–3 years of oral poly ADP-ribose polymerase (PARP) inhibitor treatment [15–17], which has led to an unprecedented 70% reduction in the 7-year risk of cancer recurrence or death in patients with *BRCA-*associated advanced ovarian cancer compared to placebo [18] and improvements in progression-free and overall survival in patients with homologous-recombination-deficient ovarian cancers [6], reflecting a major success in precision oncology.

However, the effectiveness of PARP inhibitors, like many breakthrough treatments, comes at a cost: more than 40% of patients taking PARP inhibitors experience significant enduring fatigue. A recent meta-analysis indicated that PARP inhibitors are associated with a 2.23 relative risk of high-grade (more severe) fatigue compared with placebo [19]. In our qualitative study, patients described PARP inhibitor-associated fatigue as unrelenting and pervasive, interfering with work, family, and social events, and eroding their sense of self [20]. In contrast to fatigue caused by time-limited chemotherapy or radiation, patients with advanced ovarian cancer must take oral PARP inhibitors once or twice daily (depending on regimen) for years. Because PARP inhibitors were first FDA approved in 2014, their fatigue effects are better characterized than more emerging treatments, establishing a strong scientific foundation for addressing them.

Meta-analytic evidence to date shows that after primary cancer treatment, cognitive behavioral therapy (CBT) is more effective for reducing cancer-related fatigue than other interventions (pharmacologic, exercise, other psychological) [12]. Patients with advanced cancers more frequently experience enduring fatigue than those with early-stage cancers [9]—yet the same meta-analysis found that fewer than 10% of studies have tested interventions for patients with advanced disease [12]. Further, improvements in fatigue were significantly smaller for patients with advanced disease compared to those with early-stage disease. A separate Cochrane systematic review and meta-analysis of fatigue interventions for patients with advanced cancer (most included early-stage survivors but they examined the subgroup with advanced cancer) [4] demonstrated significant reductions in fatigue only at first follow-up, but not post-intervention or the second follow-up, indicating a response that was not sustained. In addition, fatigue *interference* was not examined. Overall, the evidence was rated “very low quality” and likely biased due to small sample sizes (typically fewer than 50 advanced cancer patients per study arm).

The only known published fully powered randomized trial of an intervention to address fatigue in patients with advanced cancer used a variant of CBT to address fatigue interference in patients with metastatic breast cancer [21]. Although this trial makes an important contribution, it focused exclusively on breast cancer, the area in which most fatigue research has been conducted [12], and did not focus on fatigue interference caused by novel treatments such as PARP inhibitors. Finally, to our knowledge, very few studies have investigated whether addressing fatigue boosts cancer treatment adherence – a critically important question to advance both science and clinical practice. The current trial addresses these important gaps in a well-powered, high-quality CBT trial that addresses fatigue or its interference in the lives of patients with advanced ovarian cancer.

### The current intervention approach and pilot findings

This trial evaluates *REVITALIZE*, an intervention our team developed based on Acceptance and Commitment Therapy (ACT) [22, 23]. ACT is a variant of CBT that combines acceptance, mindfulness, and behavior-change strategies to help people cope – especially with problems that may not resolve [24, 25]. We systematically adapted ACT to address fatigue and fatigue interference challenges by first conducting a qualitative interview study among patients with advanced ovarian cancer on PARP inhibitors (*n* = 23) to understand fatigue’s impacts on daily life [20]. Participants described profound, life-limiting fatigue. For example, one participant said, “I worked at my job for over 30 years.outside, running around…and now I’m only working two hours a day…” (p. 230). Due to PARP inhibitor-related fatigue, several patients had to retire early. Another said, “You feel like ‘God, I’m so tired of being tired.’ And you don’t know where the end is…because it’s not really in sight. And it’s like ‘Oh God, I’m going to feel like this the rest of my life?’” (p. 231). Based on these findings, we developed *REVITALIZE*, an ACT-based 1:1 (individually delivered) intervention to address fatigue and fatigue interference caused by ongoing advanced cancer treatment.

In contrast to mastery and control-based behavioral interventions designed to minimize or eliminate symptoms [26], *REVITALIZE* adapts ACT to help advanced cancer patients cope with the enduring challenge of remaining on fatiguing treatment by reducing fatigue interference on their daily quality of life [24]. *REVITALIZE* helps patients with advanced cancer shift how they experience and cope with ongoing fatigue by actively accepting their experience of fatigue rather than spending precious energy trying to control, eliminate, or avoid it, by regulating their sleep rhythms to prevent fatigue worsening, and by reinvesting their limited energy to pursue, in a balanced way, what brings them vitality and meaning.

We conducted a pilot randomized trial of a weekly 6-session *REVITALIZE* intervention (with a 1-month booster session) relative to an education control (*n* = 44). Findings demonstrated strong feasibility, acceptability, and significant reductions in fatigue interference, severity, and catastrophizing, as well as improvements in quality of life and PARP inhibitor adherence following *REVITALIZE* relative to the education control condition [27]. In exit interviews, both *REVITALIZE* participants and study interventionists reported a desire to extend the intervention by several sessions to improve pacing, increase practice opportunities, and add another booster session. Thus, the current trial will test an 8-session version of *REVITALIZE* (plus booster sessions 1 and 2 months later) relative to an education control condition.

For accessibility, particularly in rural areas, and to reduce transportation burden on participants, *REVITALIZE* is designed for delivery via online videoconferencing. In the pilot trial, we developed and refined visual slides for each *REVITALIZE* session and a patient workbook that illustrates key intervention concepts and skills for both in-session and at-home practice.

### The current study protocol

This protocol describes a two-arm, prospective randomized controlled trial (RCT) to evaluate the efficacy of the *REVITALIZE* intervention in reducing fatigue interference and improving adherence to PARP inhibitors, compared with an education-enhanced usual care condition (EUC). Participants will be patients with advanced ovarian cancer who report moderate to severe fatigue (score of ≥ 4 on the Fatigue Symptom Inventory-3 screen [28, 29]) while on PARP inhibitors. This trial addresses four limitations of prior cancer-related fatigue research by: (1) focusing exclusively on patients with advanced cancer; (2) targeting fatigue associated with a novel precision oncology treatment (PARP inhibitors); (3) primarily targeting fatigue interference, a more realistic main target than fatigue severity among patients with advanced cancer requiring ongoing treatment that causes fatigue; (4) directly testing whether addressing fatigue improves cancer treatment adherence – an underexplored relationship that could inform clinical care.

Comparing *REVITALIZE* to an EUC condition helps to determine if *REVITALIZE* offers benefits beyond those realized by offering standardized cancer survivorship materials developed by the National Cancer Institute [30]. The aims of this study include:

Test the hypothesis that *REVITALIZE*, relative to EUC, will reduce the primary outcome of fatigue interference and reduce fatigue severity and catastrophizing and increase fatigue self-efficacy and quality of life (secondary outcomes).Assess whether *REVITALIZE*, relative to EUC, improves monthly PARP inhibitor adherence, dose interruptions, reductions, and persistence, using wireless medication adherence monitors and medical chart review.Test *REVITALIZE* theory-driven mechanisms of action; specifically, to see if *REVITALIZE* increases acceptance and alignment with values more than EUC, and whether changes in these putative mechanisms predict fatigue-related and quality of life outcomes at follow-up.

## Methods/design

### Study design and funding

This study is a two-arm, prospective RCT that aims to randomize 240 patients with advanced ovarian cancer who are currently prescribed PARP inhibitors and report moderate to severe fatigue. Participants are individually randomized 1:1 to either *REVITALIZE* or EUC based on a randomization block sequence generated by the study biostatistician ([name]) using R statistical software [31], stratified by PARP inhibitor type and regimen (once versus twice daily and with versus without bevacizumab) and recruitment site. Patient-reported outcomes will be collected in Research Electronic Data Capture (REDCap) [32], a HIPAA-approved, secure, web-based tool, at five timepoints: baseline (pre-intervention), mid-intervention (8 weeks after baseline), post-intervention (13 weeks after baseline), and 20- and 28-week follow-ups (FU). The 20-week FU serves as the main endpoint, and the 28-week FU serves to assess maintenance or change in effects over time. Adherence outcomes will be assessed via Wisepill, a wireless adherence tracking device [33] and medical chart review.

The study was pre-registered with identifier NCT06710548 on Clinicaltrials.gov on November 29, 2024, before enrolling the first patient (https://clinicaltrials.gov/study/NCT06710548). Dana-Farber Cancer Institute serves as the single IRB overseeing the study and informed consent is obtained from all individuals prior to study enrollment.

### Study eligibility criteria

#### Inclusion criteria

Adult (age ≥18 years), English-speaking patients with advanced ovarian cancer will be eligible to participate if they:

Have epithelial ovarian cancer (including ovarian, fallopian tube, and primary peritoneal cancers, all of which are treated as ovarian cancers).Are being treated with PARP inhibitors as a maintenance therapy after completion of first-line treatment or platinum-sensitive recurrent disease, and have taken the PARP inhibitors for at least 2 months. This corresponds to the time period when patients frequently undergo dose reductions, delays due to symptoms and side effects, and switches to other PARP inhibitors. After 2 months, most patients are on a stable dose that can be continued for the duration of their treatment.Anticipate continued treatment on a PARP inhibitor for at least 8 months at time of consent (e.g., beyond the duration of the study).Report an average rating of ≥ 4 (range 0–10) on the first 3 items of the Fatigue Symptom Inventory [28, 29], which rates fatigue levels during the past week on the most and least fatiguing day and on an average day. We used this same cutoff score in the REVITALIZE pilot study [27].Report a rating of 0 to 2 on the Eastern Cooperative Oncology Group Performance Status Scale (ECOG) performance status at time of consent [34], indicating that they are out of bed most of the day.Are capable at time of consent of understanding and voluntarily consenting to the study, attending online sessions, and completing homework for the intervention, which includes engaging in valued activities. Also, are willing to use a wireless electronic pillbox for PARP inhibitor medication.Complete the baseline (pre-intervention) survey.

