#### PARP inhibitor adherence assessment (Aim 2)

To assess monthly PARP inhibitor adherence and non-persistence, we will use Wisepill, a simple wireless electronic pillbox monitoring device (4.3”x1.8”x.5”) that sends real-time data to a protected online server when opened. This enables quick identification of any device issues and transmitting full data even if devices are not returned. Wisepill is highly reliable, acceptable, and easy to use [52–55]. It shows similar reliability as MEMS caps [56], greater accuracy than real-time reporting [57], pill counts or self-report [35, 56, 58], and direct association with biologically-measured adherence markers [57]. We used Wisepill to assess anti-cancer medication adherence in prior work [35, 52, 59]. This work established successful procedures for the remote delivery, instructions, and return of Wisepill monitors using post mail that we use in the current study. Study RA’s also complete a phone orientation with each participant to instruct them on how to use the Wisepill and confirm that it is working properly.

Wisepill adherence tracking device data will compute monthly PARP inhibitor adherence as the percent of days per 30-day month that the tracking device is opened once for each dose prescribed that day, divided by 30, using recommended methods for Wisepill data preparation and analysis [53]. PARP inhibitors that are taken once daily will require one Wisepill opening to be considered adherent on that day, whereas PARP inhibitors taken once in AM and once in PM will require two Wisepill openings at separate times to be considered adherent on that day. (As noted above, we stratify by PARP inhibitor regimen to take into account dosing schedules across study arms).

Wisepill-assessed monthly adherence will serve as the main adherence outcome. Wisepill, along with medical chart review, will also assess PARP inhibitor non-persistence, measured as stopping the PARP and not restarting through study end. Finally, medical chart review will be used to evaluate PARP inhibitor dose reductions and interruptions, the latter defined as breaks in PARP inhibitor use that reflect stopping and starting again during the study rather than stopping through study end, and disease progression events.

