### Power and sample size estimation

We plan to enroll a total of 240 patients (approximately 120 per condition) in the study. Based on findings from the *REVITALIZE* pilot study and our recent RCT for adults with advanced cancer [25], we anticipate 20% missing data at 20-week FU. Accordingly, we expect data from 192 patients (*n* = 96 per group) to be available for the primary analysis of the primary endpoints for each Aim.

For Aim 1, the primary analysis will use a two-sample t-test. With a sample size of 192, the study will have 80% power to detect a significant intervention effect corresponding to Cohen’s d = 0.41 (a small-to-moderate effect size) at a two-sided alpha level of 0.05, and 94% power to detect a moderate effect size (d = 0.50). These thresholds are smaller than the effect sizes observed in the pilot trial [27], where the primary endpoint yielded approximately an effect size of d = 0.94 for the *REVITALIZE* intervention group versus EUC at follow-up, and the targeted secondary endpoints yielded effect sizes of d≥0.60. Thus, the planned sample size provides sufficient power to detect clinically meaningful effects for Aim 1.

For Aim 2, the primary analysis for chart review data will use Fisher’s exact test. With a sample size of 192, the study will have 80% power to detect an intervention effect corresponding to Cohen’s h = 0.4 (a small-to-medium effect size) at a two-sided alpha level of 0.05, and 93% power to detect a moderate effect size (h = 0.5). The longitudinal outcomes, assessed using monthly Wisepill adherence data, provide even greater statistical power than the chart review outcomes because they involve repeated continuous (rather than single binary) measurements. Accordingly, we consider the study to be adequately powered for the outcomes specified in Aim 2 [63].

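### The chart-review power in Aim 2 overstates what Fisher's exact test delivers at 96 per arm, and the claim that Aim 2 is adequately powered depends on an event rate the protocol does not give

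*Protocol article*

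**What the plan says.** Under Inclusion criteria, patients must "have taken the PARP inhibitors for at least 2 months". The reason given is "This corresponds to the time period when patients frequently undergo dose reductions, delays due to symptoms and side effects, and switches to other PARP inhibitors", followed by "After 2 months, most patients are on a stable dose that can be continued for the duration of their treatment". A separate criterion reads "Anticipate continued treatment on a PARP inhibitor for at least 8 months at time of consent", which the protocol describes as longer than the study itself.

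Aim 2, in the section on the current study protocol, asks whether REVITALIZE "improves monthly PARP inhibitor adherence, dose interruptions, reductions, and persistence, using wireless medication adherence monitors and medical chart review". The section on adherence assessment ranks these outcomes: "Wisepill-assessed monthly adherence will serve as the main adherence outcome". Reductions and interruptions come from chart review, and non-persistence from Wisepill together with chart review.

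Under Power and sample size estimation, 240 patients less 20% missing data leaves 192, or 96 per group. Fisher's exact test is named for chart-review data, with 80% power at h = 0.4 and 93% at h = 0.5, two-sided alpha 0.05. No control-arm event rate accompanies these values. The paragraph adds that the repeated Wisepill measurements give greater power still, and ends "we consider the study to be adequately powered for the outcomes specified in Aim 2".

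**The concern.** There are two linked problems with the power statement.

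First, the power of Fisher's exact test is not a function of h alone. The test is conservative, and more so when events are few. A single figure per value of h, with no base rate, is what an arcsine normal approximation produces, not what the named test delivers.

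Second, h conceals how large an effect it represents. The protocol calls h = 0.4 small to medium, but when events are uncommon the same h means removing most of them. The protocol's only statement about dosing after entry suggests that reductions and interruptions become less frequent, and the power section does not take this up.

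What is at stake is how a null result is read. If reductions, interruptions or non-persistence show no significant difference in a trial declared adequately powered for them, readers may conclude that treating fatigue does not help patients stay on dose, when the test may have had little chance of showing it.

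**Working it through.** **Inputs from the protocol article.** n = 96 per arm (240 × 0.8 = 192; 192/2 = 96); two-sided alpha 0.05; h = 0.4 and 0.5; Fisher's exact test.

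**Assumed input.** The control-arm event rate p1, because the protocol gives none. A range is shown.

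**Step 1: reproduce the stated figures.** The arcsine approximation is power = Φ(h·√(n/2) − 1.96), with √(96/2) = 6.928.
- h = 0.4: 0.4 × 6.928 = 2.771; Φ(2.771 − 1.960) = Φ(0.811) = 79.1% (stated 80%).
- h = 0.5: 0.5 × 6.928 = 3.464; Φ(3.464 − 1.960) = Φ(1.504) = 93.4% (stated 93%).

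The stated values are therefore arcsine values.

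**Step 2: power of the named test.** For each p1, the intervention rate that gives effect h is p2 = sin²(arcsin√p1 − h/2). Exact power is the sum of binomial probabilities over all pairs of event counts that the two-sided Fisher test rejects at 0.05. Searching over control rates at 96 per arm, the maximum is 75.0% at h = 0.4 and 91.5% at h = 0.5. No control rate gives the stated 80% or 93%.

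**Step 3: what h = 0.4 means at assumed control rates, and power for a halving (exact Fisher, 96 per arm).**

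| Control rate (assumed) | REVITALIZE rate for h = 0.4 | Power at h = 0.4 | Power if the rate is halved |
|---|---|---|---|
| 40% | 21.7% | 74.7% | 83.0% |
| 30% | 13.7% | 74.2% | 65.6% |
| 20% | 6.8% | 72.4% | 42.5% |
| 15% | 3.9% | 70.3% | 29.7% |
| 10% | 1.5% | 65.4% | 18.1% |
| 5% | 0.07% | 33.3% | 6.2% |

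The lowest control rate at which h = 0.4 exists is sin²(0.2) = 3.95%. Below that, preventing every event would not reach it. At 10%, h = 0.4 is a relative reduction of (10 − 1.5)/10 = 85%. Halving the rate reaches 80% power only from a control rate of about 38% to 39%.

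**Step 4: sensitivity to sample size.** If charts were available for all 120 per arm, Fisher power at h = 0.4 would be 82.4%, 77.3% and 53.5% at control rates of 20%, 10% and 5%. Power for a halving would be 51.6%, 22.2% and 8.7%.

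**The case against.** The strongest reply is that low event rates are suggested, not shown. The rationale says changes are frequent early and that most patients are stable later; it does not say later events are rare. The sample is selected for moderate to severe fatigue, which the abstract says can lead to reductions, interruptions and discontinuation. Patients treated for platinum-sensitive recurrent disease are eligible, progression during the study is foreseen, and the 8-month criterion is only an expectation at consent. All of this stands. A reader might infer that the chart-review tests will probably be null whether or not REVITALIZE works; the documents do not support that, because the rate is unknown and at a control rate of 40% a halving has 83% power.

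Three further points also stand:
- The 2-month rationale names reductions, delays and switches, not permanent stopping. For persistence the support is weaker: the remark that the dose can be continued, plus the 8-month criterion.
- Monthly Wisepill adherence is the main adherence outcome. It is a repeated continuous measure analysed by mixed-effects models, and this argument does not reach it. A reader might infer that Aim 2 as a whole is underpowered; that does not follow.
- Chart review does not depend on a returned survey, so more than 96 per arm may be available. At 120 per arm the Fisher test exceeds 80% at h = 0.4 when the control rate is 20%, but not at 10% or 5%. The protocol plans on 192 for the primary analysis under each aim, so 96 is the figure to test.

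It may also be said that h is a recognised effect size and that a condensed article may leave event rates to a fuller document. Fair, but the article itself ties specific power values to Fisher's test and draws a conclusion covering all Aim 2 outcomes. Both are statements on the page, and the first does not reproduce for the named test.

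**Conclusion.** The point holds as a correction to the power statement and the adequacy claim. At the protocol's own 96 per arm, the named test gives at most about 75% power at h = 0.4 and 92% at h = 0.5, against 80% and 93% stated. This part needs no assumption about event rates.

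The further loss does depend on the rate. It is modest at a 20% control rate (72.4%), larger at 10% (65.4%) and severe at 5% (33.3%). These rates are assumptions. The eligibility rationale points downwards for reductions and interruptions without fixing a value.

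A reader might take the eligibility criterion itself to be the flaw. The documents do not support that: the 2-month rule has a stated rationale. What is missing is a reconciliation between that rationale and the claim of adequate power. The primary outcome and monthly Wisepill adherence are untouched.

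**What to change.** 1. Restate chart-review power for Fisher's exact test at the planned number per arm, over a stated range of post-entry control rates, and give the absolute rates that h = 0.4 implies at each. If charts are expected for more than 192 patients, say so and use that number.
2. Limit the adequacy statement to monthly Wisepill adherence.
3. Report reductions, interruptions and non-persistence as risk differences with 95% confidence intervals, and state in advance that a null result on them is not evidence of no effect.

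A composite of the three events is optional. It would pool information, but it would merge events that the adherence section deliberately keeps apart, so the correction does not depend on it.

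The cost is wording in the protocol and analysis plan, and a less favourable stated power. Eligibility, sample size and data collection do not change.
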